## Abstract

**Background:**

Medical treatments have improved survival rates for paediatric brain tumour (PBT), but the condition and treatment continue to be associated with significant cognitive morbidity. Nearly all survivors will experience some degree of cognitive impairment (neurocognitive ‘late effects’) that has a cascading impact on the development of intellectual and academic skills, quality of life, mental health, vocational attainment, and functional independence. Longstanding cognitive fatigue is also a prevalent symptom for survivors of PBT and further impacts engagement with therapeutic interventions and quality of life. Cognitive rehabilitation is recommended in national healthcare guidance and frequently requested by patients and families but rarely implemented due to a limited evidence base and poor feasibility and acceptability. There are currently no therapeutic interventions for cognitive fatigue for PBT survivors.

**Aims & Objectives:**

We aim to establish feasibility, acceptability, and preliminary efficacy for strategy-based cognitive rehabilitation for PBT. The study will determine if there is benefit to feasibility and acceptability when cognitive fatigue management is integrated to cognitive rehabilitation.

**Methods:**

Thirty-six 7-17 years olds diagnosed with PBT will be recruited from Great Ormond Street Hospital. Participants will be randomised to either 1) a 12-week cognitive rehabilitation intervention with integrated cognitive fatigue management, 2) a 6-week cognitive rehabilitation intervention alone, or 3) standard care. All participants will have received neuropsychological assessment identifying difficulties with cognition and fatigue. Feasibility (e.g., attrition, retention, adherence) will be assessed through the trial. Acceptability will be measured throughout using questionnaires and interviews based on the Theoretical Framework for Acceptability and satisfaction rating scale. Preliminary effectiveness data will be gathered pre- and post-intervention using standardised measures of cognitive skills, fatigue, quality of life, % school attendance, and goal-based outcomes.

**Outcome:**

The findings will be used to determine the appropriate rehabilitation intervention for a larger, multicentre randomised controlled trial.

## Introduction

### Background & rationale

Treatment advances for paediatric brain tumour (PBT) in recent decades have substantially improved mortality rates but come at significant cost in cognitive morbidity alongside the long-term effects of the tumour itself. Up to 100% of children treated for PBT experience some degree of cognitive difficulty despite most having achieved typical cognitive development prior to diagnosis
^
1,
2
^. Risk factors for neurocognitive impairment are varied and continue to be investigated. The most consistent risk factors for neurocognitive impairment have included provision and dose of cranial radiation, younger age at treatment, shunted hydrocephalus, and cerebellar mutism syndrome
^
2,
3
^. Most children experience a constellation of long-term cognitive impairments that impact quality of life, mental health, access to education, academic and vocational attainment, and functional independence in adulthood. The most common neurocognitive impairments are in processing speed, attention, working and long-term memory, and visual-motor function which increase with time since treatment and result in the insidious secondary slowing of intellectual and academic progress over time (neurocognitive ‘late effects’), with an average loss of 18 Full-Scale IQ points by early adulthood following cranial irradiation
^
2,
4
^. Despite developments in oncology treatment protocols, survivors of common malignant tumours (e.g., medulloblastoma) remain at risk of significant neurocognitive and functional impairment into adulthood
^
5
^.

The well documented neurocognitive late effects inform the strong emphasis on neurorehabilitation in national guidance for PBT
^
6,
7
^. Interventions aimed to alleviate the burden of cognitive impairment are paramount but rarely implemented
^
8
^. Interventions to mitigate neurocognitive impairment have included lifestyle changes, pharmacological intervention, and cognitive rehabilitation
^
9
^. Cognitive rehabilitation typically involves systematic interventions to restore and/or compensate for cognitive impairment
^
10
^ including 1) massed practice on computerised cognitive training tasks (drill-based practice, e.g., Cogmed), 2) internal and metacognitive strategy-use to optimise cognition (e.g., generalisable elaborative encoding techniques such as mnemonics), and/or 3) external compensatory aids (e.g., visual reminders). Cognitive rehabilitation is almost entirely unavailable for PBT
^
11
^ with a paucity of research and poor feasibility and acceptability of trialled interventions. Drill-based computerised rehabilitation has been the focus of the small number of available studies, however, the feasibility and acceptability of this approach for PBT is low
^
12
^ and has well documented problems in poor generalisation to skills beyond the trained task (e.g., academic skills) and poor maintenance of improvements
^
13
^. The focus of drill-based interventions is typically to remediate specific cognitive deficits which can neglect the broader profile of multiple co-occurring neuropsychological difficulties common after PBT.

Rehabilitation in paediatric acquired brain injury has greatest potential when it includes internal and metacognitive strategy-use, is adapted for developmental level, and delivered within a systemic context
^
10
^. There is currently one good quality randomised controlled trial (RCT) of a cognitive rehabilitation intervention that incorporates strategy-use for PBT
^
14
^. The intervention resulted in improvements in parental report of child inattention and academic attainments, albeit with small effect sizes. The program involved strategy-use training, but also included a demanding drill-based practice component (requiring 40 hours of practice), with only 60% of participants completing the intervention. A subsequent study
^
15
^ omitted the drill-based practice and extended the strategy-use component (15 sessions, 20 hours in total), combining it with systemic support in a smaller pilot study. The power and generalisability of the findings are limited by a small sample size, however significant improvement for written expression was found along with trends towards improvement on neurocognitive measures. Participants also rated high levels of satisfaction, particularly because the intervention improved their understanding of their cognitive strengths and weakness.

Despite some promising findings for strategy-based cognitive rehabilitation, poor feasibility is reflected in generally low completion rates. Cognitive fatigue (extreme mental tiredness) is one of the most frequently reported and distressing chronic symptoms after PBT
^
16
^. Cognitive fatigue can impact adherence to interventions, as well as participation in settings where children make most use of rehabilitation strategies such as in education and activities of daily living. Despite cognitive fatigue being both common and impairing, it has been significantly overlooked in both research and clinical interventions for PBT, with very few studies conceptually distinguishing cognitive fatigue from fatigue in general. No cognitive rehabilitation intervention for PBT has addressed the high prevalence of cognitive fatigue that could predictably limit engagement and completion of rehabilitation.

There have been no published trials to date of cognitive rehabilitation interventions for child survivors of brain tumour in the United Kingdom and within the National Health Service (NHS). The Department of Health and Social Care ‘Brain tumour research: task and finish working group’ report
^
17
^ strongly advocates that research should focus on quality of life, including “living with the long-term cognitive effects of surgery and radiotherapy” (pg.21); a priority that should be “embraced by the research community and funders” (pg. 21). The proposed research study addresses this public health priority by trialling the acceptability and feasibility of an intervention to address the long-term cognitive effects of brain tumour and treatment that impact on multiple facets of survivorship and quality of life. The study will 1) assess the acceptability and feasibility of a novel cognitive rehabilitation intervention for PBT, and 2) determine whether incorporating cognitive fatigue management improves feasibility, acceptability, and patient-reported benefit.

### Theoretical approach to acceptability

Acceptability will be evaluated using the Theoretical Framework for Acceptability (TFA
^
18,
19
^). The TFA offers a robust framework for evaluating theoretically informed components of acceptability throughout and after an intervention by those who receive and deliver it. Examples of component constructs include affective attitude (the individual’s feelings about the intervention), burden (how effortful it is to participate), and perceived effectiveness (how the individual perceives the intervention to have achieved its goal).

### Theoretical approach to outcome measurement

A major aim of cognitive rehabilitation is to improve everyday functioning and quality of life. Prevailing drill-based rehabilitation seeks to achieve this through remediating specific cognitive impairment. This approach naturally lends itself to selecting performance-based neuropsychological tests as the primary outcome measure. Impairment on performance-based tests is typically identified at pre-intervention and the test is repeated post-intervention to measure the extent of remediation. This approach has been found to yield either non-significant results or small effect sizes on measures other than those very similar to the drilled task
^
13
^, and practice effects from repeated cognitive testing can confound study results
^
14
^. Strategy-based cognitive rehabilitation shifts the focus of rehabilitation away from remediating impairment to developing metacognitive and compensatory mechanisms to better manage the impact of the cognitive impairment on everyday life. Studies focused on strategy-based rehabilitation in paediatric brain injury therefore have included outcome measures related to everyday function. On recent systematic review
^
10
^, strategy-based rehabilitation predictably does not produce change on performance-based cognitive tests. However, these studies demonstrate significant and powerful improvement on functional measures such as everyday executive function skills, problem-solving, goal-directed behaviour, daily living skills, individual rehabilitation goals, and quality of life. The findings have informed the focus of outcome measurement in the current study.

### Study objectives

The overarching study aim is to establish feasibility and acceptability for a strategy-based cognitive rehabilitation intervention for PBT, and any benefit to feasibility and acceptability by integrating cognitive fatigue management. The findings will be used to determine whether the cognitive rehabilitation intervention alone, or the same intervention with integrated fatigue management should be taken forwards to a definitive RCT.

Objectives include:

1. To assess whether the proposed cognitive rehabilitation intervention design is feasible to implement and acceptable to patients.2. To assess whether feasibility and acceptability differ when fatigue management is incorporated to determine which intervention arm to take forwards to the definitive RCT.3. To measure preliminary/limited-efficacy patient reported benefit and outcomes of the intervention arms relative to standard care.4. To identify the optimal outcome measures for a larger scale RCT.5. To document any barriers to recruiting a representative sample and acceptability of randomisation.6. To identify any practical barriers to conducting an RCT intervention at the designated NHS site.

## Methods

### Patient and Public Involvement

**
*Pre-study PPI*
**

The study has been informed by over 20 years of feedback from families affected by childhood brain tumour referred to the Neuropsychology service at GOSH. The intervention was initially developed for a patient and their carer at GOSH who reported favourable outcomes. Twelve families who had recently received care within the GOSH Neuropsychology service provided feedback on the funding proposal. The feedback was highly positive and indicated a high level of demand with 11 of 12 families indicating they would be interested in taking part. Most families said that they would find it beneficial to have options for online participation and/or support with travel costs, and for sessions to fit around school hours. All feedback has been incorporated into the study design and budget. The study was also informed by a recent North Thames survey
^
11
^ of forty-five families of childhood survivors of PBT where only 2% reported being able to access dedicated cognitive rehabilitation support, and 69% stating they either definitely would have liked their child to receive it (47%) or were unsure (22%).

The Participants Information Sheets (PISs) for the study were developed using guidance and templates from the Sponsor’s Patient and Public Involvement (PPI) department and GOSH Young Person Advisory Group (YPAG) for research. The GOSH YPAG provided advice on the acceptability of the study design, use of plain English for study documents including the PIS, and recruitment practices. All advice from the YPAG has been incorporated into the study and protocol. A carer for someone treated for childhood brain tumour and healthcare service user provided further suggestions through NIHR Research for Patient Benefit (RfPB) peer review.

**
*PPI during the study*
**

A Patient/Public Advisory Group (PAG) will be established at the start of the project and chaired by the PPI lead for the research study. The PAG has been appropriately costed for the study using NIHR payment guidance. A Stakeholder Mapping exercise under the Theory of Change model
^
20
^ was completed with the Chief Investigator and PPI study lead to identify stakeholders with relevant lived experience and knowledge of brain tumour diagnosis and treatment. The PAG will include 6 members. Nine 3-hour quarterly meetings will take place across the lifecycle of the study. The content of each PAG meeting will be dependent on the project stage. The group will be involved in providing advice and/or co-production for the study, including recruitment practices, creation of materials during the study, analysis, and dissemination of research.

**Ethics and dissemination**

The study (Protocol number 22BO24 version 2, 16.12.2024) has been approved by the Camden & Kings Cross Research Ethics Committee and NHS Health Research Authority (REC reference: 24/LO/0844, IRAS Project ID: 327316, date of approval: 16/01/2025). The study is registered on ClinicalTrials.gov registry (ClinicalTrials.gov Identifier: NCT06770335, 13/01/2025:
https://clinicaltrials.gov/study/NCT06770335).

**Consent**

Documented informed consent or assent will be sought by trained and delegated members of the research team for all participants after a discussion session based on the PIS. A copy of the PIS will be provided to participants. Special considerations for informed consent with children include PISs adapted for different ages (7–11 years, 12–15 years, and age 16+ years and a parent/carer version), assent forms for under age 16 (with parental consent) and consent form for 16+ years, and new PISs (and consent where appropriate), when children move into a new age bracket during the study. Participants will be informed that participation in the study is entirely voluntary, they can decline participation without giving a reason, they can withdraw at any time without giving a reason, and not taking part will have no consequences for their ongoing healthcare. Capacity will be presumed in the first instance (as stated in the Mental Capacity Act, 2005). For adolescent participants who can provide informed consent or where a parent consenting for their child loses capacity, the participant will not continue in the study and only de-identified data will be retained.

### Study design and setting

The feasibility study employs a randomised, parallel arm design with a standard care control group (see
Figure 1: Study Flowchart).

**Figure 1. f1:**
[figure not shown]
Study Flowchart.

Thirty-six participants will be recruited and randomised to either 1) a 12-week block of intervention (cognitive rehabilitation with fatigue management), 2) a 6-week block of intervention (cognitive rehabilitation alone), or 3) 12 weeks of standard care. Randomisation will be undertaken centrally by the study team using GraphPad random assignment. Participants will be young people aged 7 years to 17 years, 11 months who have been diagnosed with a childhood central nervous system (CNS; brain) tumour, or received oncology treatment to the brain, and are current patients at Great Ormond Street Hospital for Children (GOSH). The study is a single-site study. All participants will be recruited at GOSH, with each participant completing a 14-week study period. All study procedures will take place at GOSH. Standard care at the study site consists of 1) a single feedback session on the neuropsychological assessment findings and recommendations, and 2) continuation of routine oncology medical care, as appropriate for the patient, without any neuropsychological intervention.

### Eligibility criteria

Potential participants will be invited to take part based on the following inclusion and exclusion criteria:

Inclusion criteria

1. Age range: 7 years to 17 years, 11 months.2. Received diagnosis and/or treatment/surveillance at GOSH for a childhood tumour that involved the CNS (brain) and/or oncology treatment to brain.3. Received or receiving a neuropsychological assessment/consultation at GOSH over the course of the study period or in the 48 months prior to the study period, or under active surveillance with the neuro-oncology multidisciplinary team during the study period.4. At least 6 months post-diagnosis/acute treatment (surgery and/or radiotherapy), and 3 months post-return to school, with stable disease.5. One or more scores outside of normal limits (i.e. 1 SD above or below the mean in the direction indicating difficulty) in at least one neuropsychological domain (on performance-based tests or questionnaire-based rating scales).6. Report impairment (z-score > -0.67) in fatigue on one or more subscales of the PedsQL Multidimensional Fatigue Scale.7. Capacity/competence of patient or parent/carer to provide informed consent.

Exclusion criteria

1. Completed or having another targeted formal psychological intervention for cognitive rehabilitation or fatigue in the past 6 months.2. Sensorimotor (e.g., visual-motor) impairment only on neuropsychological assessment without additional cognitive difficulty.3. Current substance misuse from self-report.4. Currently receiving formal psychiatric care for a diagnosed mental health disorder (including active suicidal ideation), excluding ADHD treatment (if a child has a diagnosis of ADHD they should be treated).5. Intellectual Disability based on a standard score of more than 2 standard deviations below the mean on a general adaptive behaviour composite and, where available, the General Ability Index of intellect.6. Patient and parent/carer is unable to communicate verbally and in written form in English.

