All interventional components are delivered by a Psychologist under the supervision of a senior Clinical Psychologist & Neuropsychologist. The full intervention is delivered over 12 weeks, inclusive of 10, 1-hour individual sessions (child and parent attends) and a separate parent and peer psychoeducational group session during each block (i.e. during the fatigue and cognitive intervention blocks). The group sessions reinforce the same psychoeducational components of individual sessions and are primarily to facilitate peer support. The cognitive rehabilitation-only intervention is delivered in a 6-week block consisting of 6 individual sessions (child and parent attends) and a parent and peer group session. Psychoeducational webinars for each block of cognitive fatigue and cognitive rehabilitation are provided to the child’s teacher/Special Educational Needs Co-ordinator (SENCo) to enhance systemic support and maximise generalisation of strategies. The intervention is delivered hierarchically with cognitive fatigue management introduced first (in the full intervention), followed by cognitive rehabilitation strategies with consideration to developmental stage of the child. The programme content and concepts (e.g., PQRST, chunking, pacing) per session are consistent across age groups, but the delivery (e.g., wording, supporting images, and consolidation activities) is adapted by age. Degree of involvement of an adult in intervention activities can be adapted according to the child’s level of development and independence.

The intervention can be delivered in face-to-face or remote format depending on participant preference. Meta-analysis
^
30
^ and review
^
31
^ of similar remote skills-based neuropsychological interventions for young people with diverse neurological conditions have recently found remotely delivered interventions have high levels of feasibility and acceptability without compromise to fidelity and efficacy. They also have the advantage of greater geographical reach and access for families who may otherwise be unable to participate
^
15,
32
^. Criteria for discontinuing the intervention includes patient request, disease relapse requiring urgent medical treatment, and where the participant becomes ineligible based on the eligibility criteria.

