Figure 1: Study Flowchart):

1. Fatigue measuresa. Primary outcome measure: Goal Based Outcome (GBO) for management of cognitive fatigue - parent & child
^
36
^
b. Secondary outcome measures: Multidimensional Fatigue Scale – parent and child
^
37
^, individual daily fatigue analogue scale (child), % school attendance (from school report)2. Cognitive measuresa. Primary outcome measure: GBO for management of cognitive difficulty – parent and child
^
36
^.b. Secondary outcome measures: Behaviour Rating Inventory of Executive Function – second edition (BRIEF-II) – parent and teacher, PedsQL Core + Brain Tumour Cognitive Problems module – child and parent
^
38
^, The Brief Illness Perceptions Questionnaire – child
^
39
^

These outcomes measures were selected due to their psychometric properties, suitability to the aims of strategy-based cognitive rehabilitation, and precedence and sensitivity to detecting change after rehabilitation interventions
^
22,
29,
40–
44
^. The MDFS was selected as an outcome measure for cognitive fatigue as it is the only fatigue measure that compartmentalises fatigue into subdomains. In our clinical experience of this population, sequelae of cognitive fatigue are often reflected across the domains of the MDFS (e.g., problems starting and finishing activities, feeling tired or napping after cognitive activities) but with higher scores within the cognitive domain. We will evaluate this profile in the final sample to inform if and how this measure should be used in an RCT. Where measures are protected by copyright (PedsQL Multidimensional Fatigue Scale, Core module, and Brain Tumour module, and the BRIEF-II) the appropriate license agreement has been obtained for use within the study.

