The justification for the sample size comes from the NIHR Research Design Service (RDS) London evidence for sample sizes for feasibility studies (
https://www.rds-london.nihr.ac.uk/resources/justify-sample-size-for-a-feasibility-study/) and associated evidence for estimating a standard deviation to power the future definitive trial. There is no formal way to power a standard deviation estimate which is a measure of variability, therefore various rules of thumb have been developed that the sample size for a feasibility trial should be between 24–50
^
46,
47
^. A sample size of 36 (12 participants per arm of the study) is further justified by the feasibility and the precision this provides in estimating the mean and the variance
^
46
^. This can then be used to calculate power for a more precise hypothesis for a definitive randomised controlled trial.

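### Inclusion criterion 6 prints the fatigue cut-off as z > -0.67, which takes in about three quarters of the reference distribution and so cannot define impairment whichever way the scale is scored

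*Protocol article*

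**What the plan says.** Protocol article, Eligibility criteria, inclusion criterion 6: "Report impairment (z-score > -0.67) in fatigue on one or more subscales of the PedsQL Multidimensional Fatigue Scale". No other section restates or corrects the cut-off, and none defines the scoring direction of the fatigue scale.

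Neighbouring thresholds do carry a direction. Inclusion criterion 5 asks for a score "1 SD above or below the mean in the direction indicating difficulty", and exclusion criterion 5 uses a score "more than 2 standard deviations below the mean on a general adaptive behaviour composite". Criterion 6 has no such wording.

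The abstract (Methods) describes the intended population: "All participants will have received neuropsychological assessment identifying difficulties with cognition and fatigue".

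Under Preliminary outcome measures, the authors remark from clinical experience that the effects of cognitive fatigue show across the domains of the scale, "but with higher scores within the cognitive domain".

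The Intervention section lists, among the criteria for discontinuing the intervention, the case "where the participant becomes ineligible based on the eligibility criteria".

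**The concern.** A cut-off labelled as impairment should pick out one tail of the reference distribution. The printed expression picks out everything except the lower tail. It contains the mean and every above-average score, so it conflicts with the word it is meant to explain.

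Criterion 6 is the only criterion that requires fatigue to be present. Objective 2 asks whether adding fatigue management changes feasibility and acceptability, and the answer decides which arm goes forward to the definitive trial. If the rule were applied as printed, some children in the 12-week arm could receive the fatigue block with little fatigue to manage. With 12 children per arm, a few such children would matter to what the study says about fatigue management and to the fatigue standard deviations carried forward. Acceptance rates and reasons for ineligibility are themselves feasibility measures, so a misdirected criterion would also affect those counts.

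**Working it through.** **Inputs from the protocol.** Cut-off -0.67, inequality *greater than*, met on at least one subscale (Eligibility criteria, criterion 6).

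**Assumptions, not in the protocol.** Z-scores standard normal in the reference population; three subscales; equal correlation r between subscales of 0.3 to 0.7 (0 as an extreme); where stated, a population mean shifted 1 SD towards fatigue.

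**Step 1: one subscale.** The 25th centile of the standard normal is -0.674, so -0.67 is close to the lower quartile.

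- Printed rule: P(Z > -0.67) = 1 - Φ(-0.67) = 1 - 0.2514 = 0.7486.
- Mirrored rule, lower = worse: P(Z < -0.67) = 0.2514.
- Equivalent rule, higher = worse: P(Z > +0.67) = 0.2514.

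The last two each select a quarter of the reference population, as an impairment cut-off near a quartile would. The printed one selects three quarters.

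**Step 2: both scoring directions.**

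- *Lower z = more fatigue.* The sign fits and the inequality is reversed. A child is excluded only if every subscale is at or below -0.67.
- *Higher z = more fatigue.* The inequality fits and the sign is wrong. The cut-off lies on the unimpaired side of the mean.

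Neither direction makes the printed expression a definition of impairment.

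**Step 3: at least one of three subscales, reference population (illustration).** The printed rule admits 1 - P(all three ≤ -0.67). If independent, this is 1 - 0.2514³ = 1 - 0.0159 = 0.984. The mirrored rule admits 1 - P(all three ≥ -0.67). The correlated cases use the multivariate normal.

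| r | Printed rule admits | Mirrored rule admits |
|---|---|---|
| 0.3 | 95.4% | 51.2% |
| 0.5 | 92.6% | 46.5% |
| 0.7 | 88.8% | 41.1% |

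**Step 4: lower = worse, population mean -1 SD (illustration).**

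| r | Printed rule excludes (low on all three) | No subscale below -0.67, yet admitted | Mirrored rule admits |
|---|---|---|---|
| 0.3 | 32.8% | 10.4% | 89.6% |
| 0.5 | 38.3% | 14.6% | 85.4% |
| 0.7 | 44.4% | 19.7% | 80.3% |

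The third column is a share of all children. As a share of those admitted it runs from 0.104/0.672 = 15% to 0.197/0.556 = 35%.

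**Step 5: parent and child forms.** The scale has both, and criterion 6 does not say which counts. If any of six scores could qualify a child, at the same correlations, the excluded share in Step 4 falls to 17% to 35%.

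**The case against.** The strongest reply is that this is a slip of notation. The operative words ask for reported impairment, and the z-score is a gloss in brackets. The abstract and the adjacent criterion 5 make the intent recoverable. Screening is done within the neuropsychology service and repeated in full after consent, and nothing shows that anyone would count an average score as impairment. All arms share the criterion, so the randomised comparison is not biased; only the population studied could differ from the one intended. All of this stands. It makes literal application less likely, but it does not make the printed threshold correct.

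The percentages are also open to challenge. They rest on an assumed number of subscales and assumed correlations. The reference-population figures do not describe brain-tumour patients, in whom the protocol says fatigue is common. Even the mirrored rule admits 41% to 51% of a reference population, because one subscale is enough. This stands too, so the figures are illustrations only.

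Three stronger readings are tempting, and the document does not support them:

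- *The most fatigued children are excluded.* This needs lower = worse, which the negative sign suggests but no section states, and it affects only children low on every subscale.
- *The protocol contradicts itself on scale direction.* The remark about higher scores in the cognitive domain is informal, names no metric, and may simply mean more problems.
- *Fatigue effect sizes could come out with the wrong sign.* Nothing shows that the outcome would be scored against its published convention, and scoring detail may sit in the analysis plan, which is not shown.

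**Conclusion.** The point holds as an error in an operative eligibility threshold. The printed rule covers 74.9% of the reference distribution on one subscale, includes the mean, and fails to define impairment in either scoring direction. That conclusion needs only the normal reference implied by a z-score.

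Which element is wrong depends on a scoring direction that the article does not give: the inequality if lower is worse, the sign if higher is worse. Exclusion of children low on every subscale follows only in the first case. Under the assumptions in Step 4 it would reach about a third to under a half of a population shifted by 1 SD, and less if either form of the scale may qualify a child.

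A notation slip is the likeliest explanation, and there is no evidence that children were screened on the literal wording. It still needs correcting, because a site, auditor or replicator can apply only what is written. The discontinuation criterion in the Intervention section also refers back to the eligibility criteria, so the two sections must be reconciled.

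**What to change.** 1. State once which direction of the fatigue z-score means more fatigue.
2. Reword criterion 6 so that inequality and sign agree with impairment, for example at least 0.67 SD from the mean in the direction indicating more fatigue, on the pattern of criterion 5. This wording stays correct however the scale is coded.
3. Clarify the remark on cognitive-domain scores under Preliminary outcome measures so that it uses the same direction.
4. Check whether the approved full protocol carries the same wording, and reconcile the corrected criterion with the discontinuation criterion that refers to loss of eligibility.
5. Confirm from the screening log that the cut-off was applied in the intended direction.

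The cost is a one-line correction or minor amendment, a small wording change in the outcome section, and a check of the log. Sample size, randomisation and planned analyses are unaffected.
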